# Introduction

The Lower Mississippi Delta population is characterized by high levels of overweight and obesity, which are the result of long-term disruptions in energy imbalance where dietary energy intake has exceeded energy expenditure associated with physical activity. To address this issue, the overall goal of this project is to determine ways in which the *Dietary Guidelines for Americans, 2005* [DG] (U.S. Department of Health and Human Services and U.S. Department of Agriculture 2005) physical activity recommendations can be effectively adapted for the Lower Mississippi Delta population. In this study we will determine thefeasibility of adapting physical activityrecommendations by incorporating pedometers (step-counters) as self-monitoring tools within the context of an education program. Specifically, participants will be instructed to achieve DG physical activity recommendations and monitor the number of steps they take congruent with this success. Lessons learned from the feasibility study will be incorporated into the design of a future intervention in which we will conduct a properly powered, randomized controlled effectiveness trial of physical activity and adapted DG eating patterns to reduce unhealthy weight gain. An expectation from the short-term nature of the feasibility study is an immediate increase in physical activity (both number of steps and time in moderate to vigorous activity as assessed by accelerometer) based on the adopted use of a pedometer

The Pointe Coupee Parish community will be the targeted population for this study.

Goals and Objectives

The ultimate goal of this research is to achieve wider acceptance and use of the DG recommendations by the LMD population, leading to reduced prevalence of overweight and obesity and parallel reductions in the prevalence of chronic diseases and health care costs.

This feasibility study will specifically address the issue of adapting DG physical activity recommendations for the Delta population and examine the feasibility of adoption. A pedometer-based educational intervention using objective physical activity monitoring (accelerometers) will be used to assess the primary outcomes.

Hypothesis 1.Including a pedometer as a self-monitoring tool as part of adapted physical activity guidelines will result in greater immediate increases in physical activity (as measured by accelerometer) than an education program alone.

Hypothesis 2. Including a pedometer as a self-monitoring tool as part of adapted physical activity guidelines will result in a higher likelihood of achieving DG physical activity recommendations (as measured by accelerometer) than an education program alone.

Non-Hypothesis 3. Determine the number of steps (as measured by pedometer) associated with reaching the DG physical activity (as measured by accelerometer) recommendations.

**Overview of Feasibility Study**

A community site having adequate space for study measurements, completion of questionnaires and screening forms will be selected in Pointe Coupee Parish to serve as the study site for the feasibility study. The study will collect data on 60 eligible men and women residing in Pointe Coupee Parish, ages 40-64 years, and BMI of 25 to 29.9 kg/m2. Pointe Coupee Parish was chosen because it represents a typical LMD Parish in LA: a mix of rural and semi-rural populations, ethnically diverse (38% African American), and 26% of the population living in poverty (U.S. Census Bureau 2009a).

## **STUDY PROCEDURES**

**I) Baseline (Formative) Research.** During this time, we will publicly meet with community members to introduce the study. In addition, the intervention-site for the study will be determined.

**II) Study Training.** The investigators will provide training of staff for study implementation. At least one day of training will be conducted at PBRC in study procedures including protocol, consent, anthropometric measurements, dietary recalls, physical activity (including accelerometers and pedometers).

**III) Recruitment of Study Participants and Screening.** The goal for the feasibility study is to recruit a total of 60 males and females utilizing public service announcements (radio and TV), print (church bulletin announcements, and verbal announcements made by Pastors of churches in Pointe Coupee Parish during each church worship service, local community events, auxiliary meetings, word-of-mouth, presentations to various groups and organizations, and flyers (Appendix A) distributed at various businesses and churches throughout Pointe Coupee Parish. Recruitment and screening of study participants will be conducted using specific study criteria. A screening form designed to select eligible and exclude ineligible individuals will be utilized for the study. Recruitment for the feasibility study will begin on January 4, 2010 and end once 60 males and females are enrolled in the study. Baseline data collection will begin prior to the start of the study. We plan to conduct this study in Pointe Coupee Parish, LA. If we fail to achieve adequate sample sizes, we will begin recruiting subjects from adjoining Parishes, in particular, Avoyelles Parish.

**IV) Enrollment and Consent Procedure.** After screening, eligible subjects will be formally enrolled into the study. Each subject will be asked to sign an IRB-approved written informed consent form which details the purpose of study, the requirements for participation, and the potential benefits and risks. It will also indicate that participation is voluntary and may be terminated by the participant at any time. After the informed consent is obtained, baseline measurements will begin.

**V) Measurements.** All measurements will be conducted by designated staff. The following measurements will be made in all study participants as listed below:

1.General. During the recruitment phase all potential participants will complete an initial screening and study specific form to provide demographic, and health information such as age, past and present medical history. Initial screening form (Appendix B), and study specific form (Appendix C) are provided in the appendices noted.

2. Dietary Assessment. Dietary data will be collected at baseline by 24-hour recall (Appendix D)—using USDA’s Automated Multiple Pass Methodology (AMPM).

3. Anthropometric Assessment. Anthropometric assessment will consist of: measurements of height, weight, and waist circumference. With the exception of height, all other measures will be done at the beginning (baseline), and end of study. Height will be measured twice and averaged at baseline only without shoes to the nearest centimeter using a stadiometer. With the exception of height, weight will be measured twice and averaged at the beginning (baseline), and end of feasibility phase.

### **Height**

Height measurement to the nearest 0.1 cm is taken by a certified staff member using a stadiometer. Height is measured in inches with the participant standing on a firm, level surface that is at a right angle to the vertical board of the stadiometer.

Instruct the participant to remove shoes and headgear (hats and unusually large hairpieces) and to stand erect with feet flat on the floor and both heels together, touching the base of the vertical board. The participant stands erect with back, shoulder blades, and buttocks in contact with the vertical height board. If the participant cannot be positioned so that all of the above are in contact with the board, position so that the participant is standing erect with buttocks in contact with the board. The participant's weight is evenly distributed on both feet, and arms remain relaxed at the sides with palms facing inward. The participant stands facing straight ahead with his/her head in the horizontal (Frankfort) plane. The eyes of the examiner should be at the same level as the height indicator bar to obtain the most accurate measurement (Figure 1, Frankfort Horizontal Plane).

Ask the participant to inhale deeply and maintain a fully erect position without altering the load on the heels. Bring the height board down snugly, but not tightly, on the top of the participant's head. Record the height to the nearest 0.1cm.

**Figure 1. Frankfort Horizontal Plane for Measuring Body Height**

[figure not shown]

TRAGION: Notch above tragus of ear or at upper margin of zygomatic bone at that point.

FRANKFORT PLANE: Orbitale tragion line horizontal.

### **Weight**

Ask the participant to stand in the center of the scale platform, since standing off-center may affect the weight measurement. It is suggested that marks be made on the platform to insure the proper position of the participant's feet. The participant should stand with arms relaxed at the sides, head erect, and eyes looking straight ahead.

A Digital Medical Scale will be provided for weight measurements at the intervention study-site(s).

Make sure the scale reads "0" before the subject stands on the measurement platform. When the digital readout stabilizes, record the observed weight to the nearest 0.10 lbs or 0.25 kg.

All weight measurements consist of two independent weight assessments, and will be performed at baseline and end of study on each participant. Have the participant get off of the scale and then repeat the above procedure and record both weights. The computer will determine the official weight measurement after data entry. In the meantime, staff should report the approximate weight, to the nearest whole pound, to the participant.

**Waist Circumference**

**Procedure**

Instruct the participant to gather his or her shirt above the waist, cross the arms, and place the hands on opposite shoulders. Demonstrate the desired position of the arms. It may help to tell participants to think of giving themselves a hug. If necessary, lower the pants and underclothing to slightly below the waist. Again, always tell the participant what you are going to do before you do it.

Stand on the participant’s right side. Palpate the hip area to locate the right ilium of the pelvis. With the cosmetic pencil draw a horizontal line just above the uppermost lateral border of the right ilium. Cross this mark at the midaxillary line, which extends from the armpit down the side of the torso. Exhibit 3-9 shows the measurement site correctly marked for the waist circumference.

Extend the measuring tape around the waist. Position the tape in a horizontal plane at the level of the measurement mark, and ensure the horizontal alignment of the tape. Check that the tape sits parallel to the floor and lies snug but does not compress the skin. Always position the zero end of the tape below the section containing the measurement value. Take the measurement to the nearest 0.1 cm at the end of the participants.

4. Physical Activity Assessment. Study participants will be asked to respond to a physical activity readiness questionnaire (PAR-Q) [Appendix E) for safety reasons before beginning any physical activity regime. Accelerometers and Pedometers will be provided and used to measure physical activity and to increase steps.

Acceleromter Procedure

The ActiGraph accelerometer will be used to determine physical activity at baseline and at follow-up as follows:

The measurement of physical activity pattern and volume, specifically minute-by-minute participation in different intensities of physical activity. The equipment used is the ActiGraph GT3X manufactured by ActiGraph, of Ft. Walton Beach, FL ([www.theactigraph.com](http://www.theactigraph.com/)), and previously distributed as the GT1M, the 7164, the MTI, and the CSA. An ActiGraph User Manual is also available for download from this website.

Process Overview

1. Charging accelerometer
2. Initializing accelerometer (preparing the device to collect data)
3. Instructing the participant on self-monitoring procedures
4. Downloading data
5. Preparing electronic files for archiving

Procedure

1. Charging accelerometer

| - Research Nurse/Coordinator - Clinic Staff | - 1. Connect the GT3X to a standard computer USB port using the USB cord provided. Allow time for recharging. Charging time will depend on battery life but will not usually exceed 3 hours for a fully depleted battery. The GT3X will issue a single LED flash to indicate it is charging while plugged into computer.   2. Charging is complete when the LED is steady on while plugged into the computer. |
| --- | --- |

1. Initializing accelerometer (preparing the device to collect data)

| - Research Nurse/Coordinator - Clinic Staff | - 1. Initialize the accelerometer before the subject arrives.   2. If there is no desk top icon for the ActiLIfe Software, open the program through the “Start” menu by navigating to “All Programs -> Actigraph.”   3. Once the ActiLife start screen is viewable, click the Start button.   4. Plug in the GT3X to the designated USB port using the USB cord providing. Use this same USB port always for initialization and download.   5. When device is recognized, Click OK to continue.   6. On the initialization screen click GT3X Mode, Activity, Step Count, and Enable Stop Time.   7. Select a 60 second epoch.   8. Enter start date time to be the next day at 4:00am.   9. Enter the stop date time to be 7 days after the start day at 4:00am.   10. Enter the subject identifier in the subject information cell.   11. Select OK   12. Wait while initialization proceeds.   13. Disconnect the device from the computer and click OK.   14. Select an appropriately sized elastic belt (24, 36, 48, or 60 inches).   15. Lace the belt through the back of the provided pouch.   16. Place the initialized device in the pouch with the word ActiGraph at the bottom of the pouch.   17. The unit is now ready to collect data. |
| --- | --- |

1. Instructing the participant on self-monitoring procedures

| - Research Nurse/Coordinator - Clinic Staff | - 1. Demonstrate how to wear the belt on the waist. Align the ActiGraph over the right hip (mid axillary line). The unit can be worn either above or below clothing. It is not necessary for it to make contact with the skin.   2. Instruct the subject to wear the accelerometer during waking hours for 7 days, engage in usual activities, and remove the device only during any water activities (e.g., swimming, showering, and bathing)   3. Instruct them not to otherwise tamper with the device. |
| --- | --- |

1. Downloading data

| - Research Nurse/Coordinator - Clinic Staff | - 1. Choose the same computer and USB port that was used when the device was first initialized.   2. If there is no desk top icon for the ActiLIfe Software, open the program through the “Start” menu by navigating to “All Programs -> Actigraph.”   3. Click on the Download button on the start screen. If the device is not connected to the original USB port the software will indicate so.   4. Wait for downloading to complete.   5. Once complete, Click Yes to save data to file. The default destination will be C: Program Files\ActiGraph\ActiLife\Files |
| --- | --- |

1. Preparing electronic files for archiving

| - Research Nurse/Coordinator - Clinic Staff | - 1. Choose the same computer and USB port that was used when the device was first initialized and subsequently downloaded   2. If there is no desk top icon for the ActiLIfe Software, open the program through the “Start” menu by navigating to “All Programs -> Actigraph.”   3. Click on Analyze Data on the Menu bar.   4. Select Create Graphs.   5. MS Excel will load. Click on the graphic in the center of the Excel document.   6. Select the specific data file (.DAT) file on which the analysis is to be performed. It should be identifiable by the subject identifier.   7. Confirm that Text, Graph, and Cutlines are selected for Activity. Confirm that Text and Graph are selected for Step Count. Leave the Graph Titles blank.   8. Click continue. Save the output as Subjectidentifiergraphs.xls.   9. Return to the ActiLife software.   10. Click on Analyze Data on the Menu bar.   11. Select Create Caloric Output File   12. Confirm Freedson Equation is selected.   13. Select the specific data file (.DAT) file on which the analysis is to be performed. It should be identifiable by the subject identifier.   14. Name the output to be saved as Subjectindentifiercalories.csv   15. Select kilograms and enter the subject’s mass (weight) in kilograms.   16. Confirm that an MS Excel File has loaded with the name Subjectindentifiercalories.csv   17. Close the file.   18. Arrange for transfer of both files to RCG. |
| --- | --- |

A pedometer will be used in this study to encourage participants to increase their walking behavior. We will employ the Lifestyles NL1000 pedometer.

Pedometer NL 1000 Procedure

The measurement of physical activity pattern and volume, specifically steps/day and time in moderate+ activity. The equipment used is the NL-1000 distributed by New Lifestyles. An NL-1000 User Manual is also available for download (http://www.new-lifestyles.com/NL-1000_Users_Guide.pdf).

Process Overview

1. Installing the battery
2. Set modes for measurement
3. Instructing the participant on self-monitoring procedures
4. Recording data

Procedure

1. Installing the battery

| - Research Nurse/Coordinator - Clinic Staff | - 1. Use a coin to pop open the battery cover.   2. Identify the top “+” side of the battery   3. Insert the battery with the “+” side facing up .   4. Replace the battery case cover.   5. A low charge icon will appear on the digital screen when battery power is low and needs to be replaced |
| --- | --- |

1. Set modes for measurement

| - Research Nurse/Coordinator - Clinic Staff | - 1. Enter the set mode manually by pressing and holding the SET button for 3 seconds.   2. You will begin with time of the day. Press the + button until the flashing digits reflects the correct hour. Use the – button to back up. Pay attention to AM or PM to set correct time.   3. Press SET to move on to minutes. Repeat the process to set minutes.   4. Leave stride length at default 2’ 6”. Press SET to move to Real-time Display Mode. |
| --- | --- |

1. Instructing the participant on self-monitoring procedures

| - Research Nurse/Coordinator - Clinic Staff | - 1. Demonstrate how to wear the pedometer horizontally on the waist band (half way between navel and hip). It is not necessary for it to make contact with the skin. It must be horizontal (not rotated). Use the provided security strap.   2. Instruct the subject to take 20 steps and check the pedometer. It should say 19-21 steps, else move its attachment to insure correct placement (not rotated).   3. Instruct the subject to wear the pedometer during waking hours for 7 days, engage in usual activities, and remove the device only during any water activities (e.g., swimming, showering, and bathing)   4. Instruct them not to otherwise tamper with the device.   5. Instruct them on how to complete the recording form (date, time on, time off, day end steps). Ask them to record time that the instrument was removed.   6. This pedometer does not require resetting at the end of the day. It automatically resets at midnight and records the previous day’s value in its memory. |
| --- | --- |

1. Recording data

| - Research Nurse/Coordinator - Clinic Staff | - 1. When the pedometer and written record are returned quickly scan for unusual < 1000 steps or >20000 steps in a day) and missing values. Query unusual values and make notes in the Comments column.   2. When subject has left, scroll through memory function to verify written records. Press the Memory button. When indicator arrow is on Steps, two pieces of alternating flashing data are available: the day and the number of steps for that day. Day = 1 is yesterday, Day =2 is two days ago, etc. Wait for the steps accumulated for each day to flash, then press Memory to advance to the next day. Note discrepancies in the Comments column.   3. Arrange for transfer of records to RCG. |
| --- | --- |

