**Intervention Phase**

The study will take place over a period of 30 days. After randomization, participants will be assigned to either the intervention or control group. Participants will be asked about their usual diet. They will then be asked to wear an accelerometer (a device that measures physical activity and inactivity) for 7 days (one week). When they return, they will be asked about their physical activity. The next 7 days (one week), both groups will receive culturally tailored educational materials (Appendix E) about how to become physically active. Participants assigned to the intervention group will receive a pedometer along with directions about how to use it to help increase their physical activity. They will be asked to write down the number of steps taken each day they wear the pedometer. The last 7 days (one week), the intervention group will be asked to wear the accelerometer again and also a pedometer. The control group will be asked to only wear the accelerometer again. When participants in the intervention group return the accelerometers, they will be asked about their experiences over the previous few weeks. Directions and personal instructions will be provided on how to use the pedometer as a self-monitoring tool to increase the number and intensity of steps participants take each day to increase the probability of meeting the DG physical activity recommendations. Examples will be provided of walking paces that correspond to moderate-to-vigorous physical activity to help ensure that walking is undertaken at a suitable intensity**.** Self-monitoring will be enhanced by having participants keep a daily log of the number of steps they take each day when they rest their pedometer.

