**Limitations of the Intervention**

The potential limitation and/or problems to be anticipated include non-compliance and loss to follow-up. To minimize this effect, Walmart gift card in the amount of $30 will be given to all study participants.In addition, all participants will receive a pedometer to keep as an incentive.

Study Design

We will conduct a randomized controlled trial to determine the feasibility of using pedometers to cause immediate short-term increases in moderate-to-vigorous physical activity in the Lower Mississippi Delta population.

#

Subjects

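### The pedometer staff script asks the intervention arm for usual activity, which contradicts the intervention, and no time is given for handing controls their incentive pedometer

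*Protocol*

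**What the plan says.** **Pedometer script.** In the Pedometer NL 1000 Procedure, the step on instructing the participant reads "Instruct the subject to wear the pedometer during waking hours for 7 days, engage in usual activities". It names no week and no phase.

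**Accelerometer script.** The matching step reads "Instruct the subject to wear the accelerometer during waking hours for 7 days, engage in usual activities". The procedure is introduced by "The ActiGraph accelerometer will be used to determine physical activity at baseline and at follow-up as follows", and no separate wording is given for the second occasion.

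**Intervention.** Under Intervention Phase, for the week after baseline, "Participants assigned to the intervention group will receive a pedometer along with directions about how to use it to help increase their physical activity". In the last week the intervention arm wears both devices, while for controls "The control group will be asked to only wear the accelerometer again". The sentence that introduces the pedometer, just before its procedure, says that it is there to encourage more walking.

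**Participant handout (Using Your Pedometer).** The first day is to be left unchanged so that a personal baseline can be recorded. After that, the participant adds steps and aims for the resulting target daily.

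**Who receives a pedometer.** Item 4, Physical Activity Assessment, says "Accelerometers and Pedometers will be provided and used to measure physical activity and to increase steps". It falls under V) Measurements, which opens with "The following measurements will be made in all study participants as listed below". Limitations of the Intervention adds that "all participants will receive a pedometer to keep as an incentive", without a time.

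**The concern.** The randomised comparison is pedometer plus education against education alone, so the pedometer and the directions that go with it are the only planned difference between the arms. A request for usual activity is sensible in a baseline week. Given with the pedometer, it asks intervention participants not to do what the intervention asks of them. The follow-up accelerometer week supplies the outcome for both hypotheses: the change in minutes of moderate-to-vigorous activity, and the change in the percentage reaching the guideline. A wear instruction that discourages change in that week bears directly on what is measured.

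The pedometer to keep raises a second question. A control who received one before the follow-up week would have the device that defines the other arm.

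**Working it through.** The Protocol gives no power, standard deviation or compliance figure to reproduce. The check is therefore a comparison of passages, followed by algebra for direction only.

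**1. Could the pedometer script be baseline wording?** No. In Intervention Phase the first 7 days involve the accelerometer alone. The pedometer is given out for the second 7 days and worn again in the third, by the intervention arm only. Every week in which this script can apply is an intervention week.

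**2. Does the handout account for it?** Only in part. It asks for unchanged behaviour on one day and then for an increase every day. The script says 7 days. Staff cannot follow both as written.

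**3. Does the accelerometer wording reach the outcome week?** Yes. The procedure is stated to apply at baseline and at follow-up, and it contains a single instruction.

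**4. Direction of the effect.** Let D_I and D_C be the mean changes in the intervention and control arms without the usual-activity wording, with D_I above D_C and neither negative.

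- *Pedometer script (intervention arm only).* If a share f of the arm's increase is lost, the contrast becomes (1 − f)D_I − D_C. It falls by f × D_I, toward zero for moderate f.
- *Accelerometer script (both arms).* If shares f_I and f_C are lost, the contrast becomes (1 − f_I)D_I − (1 − f_C)D_C. With f_I = f_C = f it is (1 − f)(D_I − D_C), which is smaller. If controls comply more than the intervention arm, it may not shrink at all. The direction depends on relative compliance, about which the Protocol says nothing.
- *Early handover to controls.* If a share g of controls used a pedometer as the intervention arm does, the contrast would be D_I − [(1 − g)D_C + g × D_I] = (1 − g)(D_I − D_C). If handover follows return of the follow-up accelerometer, g = 0.

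**5. Size.** None of f, f_I, f_C or g is stated or can be derived. The Protocol regards a 100% increase in daily minutes as clinically significant but gives no baseline mean or standard deviation, so even a standardised effect cannot be formed. Any percentage loss would be an assumption.

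**6. Do controls use a pedometer during the study?** The specific passages indicate not. The Intervention schedule has a row for distributing and returning pedometers under the intervention group and none under the control group. Intervention Phase has controls wear the accelerometer only. The analysis of steps uses intervention-group data only, and the post-study survey has a section for the pedometer group alone. The general sentence in item 4 and the untimed incentive sentence do not override these, but they do not state the limit either.

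**The case against.** Four stronger readings are tempting, and the documents support none of them.

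- *Following the Protocol cancels the intervention.* It does not. Intervention Phase calls for personal instruction to raise the number and intensity of steps. The handout has participants set a step goal, and the take-home sheets for both devices contain no usual-activity wording. The phrase also stands between wearing the device in waking hours and removing it for water activities, so it can be read as an instruction to keep it on through the day. That reading is fair, but the literal one remains open to staff working from the script.
- *The device procedures give pedometers to everyone.* They do not. The all-participant text is the incentive sentence and the general sentence in item 4. A pedometer to keep, offered with a gift card against loss to follow-up, fits an end-of-study handover. The cell marks in the two schedule tables are missing from the text as read, so some timing may be shown there.
- *The contrast shrinks by a known amount.* No such figure can be supported. The accelerometer wording is the same in both arms, and both arms receive education to be active.
- *A null result would be uninterpretable.* This goes too far. Intervention participants log daily steps, staff check the logs against device memory, and a first-day value is recorded. These show whether steps rose. They do not show whether a failure to rise came from the script or from the pedometer, so part of the worry stands.

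**Conclusion.** The point holds as an internal contradiction in the staff scripts and an unstated handover time. The pedometer script is the firmer part: it applies only to the intervention arm, only in intervention weeks, and conflicts with the stated purpose of the device and with the handout from the second day on. The accelerometer script has the same fault at follow-up, but its effect on the between-arm difference is uncertain.

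If the wording is followed literally, the tested contrast could move toward zero. This assumes that staff give the instruction as written and that participants act on it over the other directions they receive. The amount cannot be quantified. Contamination of controls is possible because the timing is left open; nothing directs it. The design is not invalidated, but the correction is worth making because it protects the only randomised difference and costs almost nothing.

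**What to change.** Reconcile four places in the Protocol:

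1. **Pedometer NL 1000 Procedure:** delete the usual-activity phrase and refer to the self-monitoring directions under Intervention Phase, keeping the handout's unchanged first day.
2. **Accelerometer procedure:** limit the phrase to the baseline week. At follow-up, use one neutral wear instruction, identical in both arms, covering waking hours and removal for water activities.
3. **Item 4, Physical Activity Assessment:** state that accelerometers go to all participants and study pedometers to the intervention arm.
4. **Limitations of the Intervention:** state that controls receive the incentive pedometer only after the follow-up accelerometer has been returned.

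The cost is wording in two scripts and two sentences, plus covering the change in staff training. No visit, measurement or participant is added, and no activity target changes.
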